#### Physical function outcomes

Secondary physical function outcome outcomes included KOOS individual subscales, functional performance and ULCA activity score. The choice of functional performance tests was based on the recommended OARSI performance test for functional testing in OA [63]. A 4 × 10 m fast-paced walk test, timed up-and-go, 4-stair climb test and 30-s chair stand were chosen to encompass the key domains of functional activities from sit-to-stand, walking short distances, stair negotiation and ambulatory transitions. The ULCA activity score is a validated score that is recommended for use in patients with hip or knee OA [64].

#### Dietetics outcomes

In addition to Body Mass Index, Food Frequency Questionnaire (FFQ) will be collected to monitor for change in dietary habits. Modification to the original Food Frequency Questionnaire (FFQ) was performed to reduce the length and thereby responder burden and adapt it based on local dietary practices. Scoring was developed by weighting fat/sugar/fibre content of the particular food item based on the energy and nutrient composition reported by the Singapore Health Promotion Board (http://focus.hpb.gov.sg/eservices/ENCF/). Modified FFQ will only be done for patients who have a BMI > 23.5.

#### Psychological outcomes

The Pain Interference Scale (Pain intensity (P), interference with enjoyment of life (E), interference with general activity (G))(PEG) [36] is a 3 item scale developed and validated from the Brief Pain Inventory(BPI) for chronic pain measurement, particularly in chronic musculoskeletal patients. The Patient Health Questionnaire-4 (PHQ-4) [35] is a validated questionnaire that allows measurement of both anxiety and depression, both common psychological conditions associated with poorer quality of life in OA patients [38]. Patient activation is defined as an individual’s propensity to engage in adaptive health behaviour that may lead to improved outcomes [43, 44]. Activation levels are measured by the Patient Activated Measure (PAM) [37], a validated questionnaire that looks at knowledge, skills and confidence in managing health.

#### General outcomes

Quality of Life will be measured using the EQ-5D, both the descriptive index and EQ-VAS [51]. The EQ-5D value set that has been validated for the Singapore population using a time trade-off method and was used to calculate utility values [65]. It will also be used in the computation for Quality of Life Years (QALYs) and eventual cost-effectiveness.

Analgesia consumption will be measured using the Cumulative Analgesia Consumption Scale (CACS) which measures both the quantity and potency of the analgesia based on WHO analgesia ladder over a 1 week period [57].

Global perceived effect (GPE) [53] will be assessed with the question: With respect to your knee, how would you describe yourself now compared to before the treatment?? Answered on a seven-point Likert scale ranging from ‘Improved, an important improvement’ to ‘Worse, an important worsening’. Satisfaction with current knee function will be assessed by the Patient Acceptable Symptom State (PASS) [54] using the question: “When you think of your knee function, will you consider your current condition as satisfying? Answered by ‘yes’ or ‘no’. Participants not satisfied with current knee function will be asked to complete a second single-item question, relating to treatment failure (TF) at the 12-month follow-up: ‘Would you consider your current state as being so unsatisfactory that you think the treatment has failed?’. Answered by ‘yes’ or ‘no’.

Any adverse events (AE) and serious adverse events (SAE) will be collected during all follow-up visits using open-probe questioning to ensure all AE are recorded. SAE will be defined as any AE that results in hospitalization or is life-threatening. Participation in the trial for the subject will cease if a SAE occurs. Undergoing an indicated surgical procedure such as a knee arthroplasty for knee OA due to failure of non-surgical treatment will not be considered an AE. In the event of more than 3 SAE, decision to stop the trial will be considered however the final decision will be made by the Principal Investigator (PI) in conjunction with the ethics and clinical board. Provision for post-trial care and compensation will be made for subjects who suffer harm during the course of the trial.

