### Intervention – CONNACT model of care

The development and core principles of the CONNACT MoC has been described as part of the pilot study [25]. Grounded from a throughout literature search on the best practices in knee OA care [3, 26], a review of successful programs [11], international collaborations and the process evaluation patient interviews from the pilot study has allowed the CONNACT MoC to be further refined and contextualized.

The CONNACT MoC consists of a 12-week community based, individualized, multidisciplinary intervention for knee OA. In summary, the core principles are firstly a chronic disease multidisciplinary model emphasizing self-management and long term sustainable behavioural change, secondly, care stratification using a triage criterion and thirdly, implemented through a grounded community-based setting.

Table 2 outlines the intervention summary, including each component, triaging criterion, intervention principles and delivery. A full description of the intervention in accordance with TIDieR [27] and CERT [28] reporting guidelines is available in the Additional file 1. Further rationale and details for the triaging criterion and the self-management philosophy underpinning the CONNACT MoC are elaborated below.

**Table 2 Tab2:** Intervention Summary

Intervention Component	Criteria to receive intervention	Healthcare Professional	Treatment Principles	Delivery Format
Exercise Therapy	All patients	Physiotherapist	American College of Sports Medicine (ACSM) [29] and Neuromuscular Exercise (NEMEX) [30] guidelines	Group sessions × 8
Clinical Assessment and Education	All patients	Orthopaedic Surgeon Psychologist Social Worker	Clinical and Radiological Assessment Pharmacological Intervention “Expert” Patients	Group Education sessions × 2 Support Group session x 1
Dietetics and Nutrition	BMI > 23.5	Dietician	Dietary intervention to increase dietary-related nutrition knowledge and self-efficacy for effective weight loss [31]	Group sessions × 3
Psychological support	PHQ-4 > 5 or PEG > 4 on all scales or PAM < 3	Psychologist Social Worker	Acceptance and Commitment Therapy (ACT) principles [32, 33] Patient Activation [34] Pain Management Coping Strategies and improving compliance to behavioural modifications	Group sessions × 3

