#### Self-management philosophy

Self-management is a key foundation for the CONNACT MoC. This will be achieved through several methods. Firstly, through the program content. The education and psychology classes grounded in the principles and psychological model of Acceptance and Commitment Therapy (ACT) [32, 33] and Patient Activation [34] strategies which have been shown to the effective. In particular, there has already been evidence to show the effectiveness of ACT in the local chronic pain population in Singapore [46].

Secondly, through the program delivery format. The program’s duration of 12 weeks is based on current evidence of the time taken for a habit to form [47]. The program is structured as a weekly class with a gap of 3 weeks between week 8 and week 12 factored in to allow patients the opportunity to incorporate these behavioural modifications as part of their daily routine before returning for the final session on week 12. In addition, after each session, patients will be given “homework” and exercises to perform at home and are reviewed at the next class. This combination of class-based and home-based individual treatment has been shown to be effective in knee OA [48]. In addition, group or class-based interventions have also been shown to be more effective compared to pure individual interventions in promoting physical activity through cohesion and peer support [49]. A flexible post-intervention program will be available for patients who would like to continue to exercise together in a group and social network platforms e.g. Whatsapp group chats or Facebook groups will also be utilized to facilitate patient group interaction throughout and post-intervention. In addition, a support group session 3 months after program completion will be arranged for reinforcement for key concepts and continued promotion of group interaction.

Thirdly, through the use of “expert patients”. These “expert patients” are patients who have previously completed and benefitted from the CONNACT program. They will be invited to volunteer and share their experiences and advice as part of the education class to serve as a role model for patients. “Expert patients” been successfully incorporated in other knee OA programs before [30].

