### Outcomes

The choice of outcome measures is based on the OARSI guidelines for lifestyle diet and exercise clinical trials in OA [50]. The recommended core outcomes are pain, physical function, global patient assessment and mobility. Additional outcomes include health-related quality of life and global physician assessment. The outcome measures will be collected at baseline, 3, 6 and 12 months. Table 3 summarizes all the outcome measures and Additional file 4 outlines the different data collection steps based on the SPIRIT guidelines.

**Table 3 Tab3:** Outcome Measures Overview

Effectiveness Measures				Compliance and Adherence Measures
Physical Function	Dietetics	Psychology	General	
KOOS_4_	Body Mass Index (BMI)	Patient Health Questionnaire 4 (PHQ-4) [35]	Quality of Life EQ-5D [51]	Appointment default rate
KOOS individual subscales	Semi-Quantitative Food Frequency Questionnaire (FFQ) [52]	Patient Activation Measure (PAM) [37]	Global Perceived Effect (GPE) [53]	Exercise Adherence Questionnaire
Functional Performance 1. Timed up-and-go 2. 4 × 10 m face paced walk test 3. 4-stair climb test 4. 30s chair stand		Pain, Enjoyment, General Activity Scale (PEG) [36]	Patient Acceptable Symptom Score (PASS) [54]	Sports Injury Rehabilitation Adherence Scale (SIRAS) [55]
UCLA activity score [56]			Analgesia Consumption [57]	
			Adverse events	

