#### Compliance and adherence

Compliance and adherence are key aspects in any exercises-based intervention for MSK conditions and having compliance measures allows for a more accurate interpretation of the results and form a significant part of the process evaluation [66]. Unfortunately, there is no specific measure for exercise adherence that has been proven to be high quality, relevant and acceptable [67]. In order to give a holistic picture to adherence, the Sports Injury Rehabilitation Adherence Scale (SIRAS) [55] will provide the healthcare providers perspective while a self-administered questionnaire for patients has been designed to obtain patient’s input (Additional file 2). SIRAS is a 3-item instrument that assesses patient’s intensity to exercise, the extent to which instructions were followed and receptiveness to change during each rehabilitation session. SIRAS will be done after each physiotherapy session and the exercise adherence questionnaire will be done at 3, 6 and 12 months. These adherence measures will only be performed in the intervention arm patients due to the variability of treatment delivery in the usual care arm. Non-compliance will be defined as less than 75% attendance of the prescribed treatment in the intervention arm. For usual care, the number of physiotherapy sessions will be at the discretion of the patient; thus, no non-compliance cut off limit will be set.

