### Cost estimation and outcome measurement

Cost data will be collected via hospital administrative databases and patient-reported questionnaires to estimate direct medical, direct non-medical and indirect costs. Indirect costs include health-related productivity loss due to knee OA [70] from absenteeism and presenteeism, measured with the Work Productivity and Activity Impairment Questionnaire (WPAI) [71]. The scope of the cost data collection was based on the validated OA Cost and Consequences Questionnaire (OCC-Q) [72] and adapted to the Singapore context to ensure that all relevant sources of cost were collected. The cost questionnaire used can be found in Additional file 3. Cost data will be collected at 3 monthly intervals till 1-year follow-up.

The primary measure of health benefit will be Quality of Life Years (QALYs) measured using the EQ-5D [51]. The incremental cost-effectiveness ratio (ICER) over the trial period of this multidisciplinary non-surgical community-based program for knee OA compared to usual care will be determined.

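### The only adverse-event collection the article states is questioning at the 3-, 6- and 12-month visits; data already planned for costing would shorten recall and serve both arms alike

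*Protocol article*

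**What the plan says.** Under General outcomes the protocol article gives the method, the occasion and the purpose of safety data collection in one sentence: "Any adverse events (AE) and serious adverse events (SAE) will be collected during all follow-up visits using open-probe questioning to ensure all AE are recorded". Table 3 lists adverse events among the outcome measures, and the Outcomes section fixes the schedule: "The outcome measures will be collected at baseline, 3, 6 and 12 months".

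General outcomes then defines an SAE by hospitalisation or threat to life and attaches two consequences to it. The patient's participation ends when an SAE occurs, and stopping the trial is considered after more than three SAEs.

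On exposure, the intervention section says: "The CONNACT MoC consists of a 12-week community based, individualized, multidisciplinary intervention for knee OA". The Self-management philosophy section adds: "The program is structured as a weekly class with a gap of 3 weeks between week 8 and week 12". The one session-level measure described is an adherence scale, used in the intervention arm only: "SIRAS will be done after each physiotherapy session". Under Usual care, the number of physiotherapy sessions is left to patient and therapist.

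The economic component plans two further data flows. Their sources are: "Cost data will be collected via hospital administrative databases and patient-reported questionnaires". Their timing is: "Cost data will be collected at 3 monthly intervals till 1-year follow-up". Neither is mentioned as a source of safety data.

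**The concern.** The stated collection points are sparse where timing matters most. The first comes at about the end of the supervised programme, so an event in an early week may not be asked about until some months later. The last interval is six months long, and patients forget or misdate events over such a period. Open questioning is active enquiry, but it still depends on what the patient remembers and chooses to mention.

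Two things are at stake. First, both SAE rules presuppose that SAEs become known reasonably soon, and the collection sentence supplies no means of learning of them between visits. Second, adverse outcomes are a reported comparison: they are in Table 3 and again under Effectiveness in the RE-AIM table. If staff pick up events informally between visits, they will do so more often in the CONNACT arm, which has scheduled classes, than in usual care, which has no fixed number of sessions. Reporting could then differ by arm for reasons unrelated to harm.

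**Working it through.** The plan gives no figure for this point, so there is none to reproduce. The check is calendar arithmetic on the stated schedule.

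**Inputs.** Visits at 3, 6 and 12 months (Outcomes). Programme length 12 weeks (intervention section). Cost collection every 3 months to one year, hence 3, 6, 9 and 12 months (Cost estimation and outcome measurement). Planned recruitment 100 patients (Sample size calculation). Assumptions: the programme starts at baseline, and events are spread evenly over the 12 months.

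**First visit against end of programme.**
- Programme end: 12 × 7 = 84 days.
- 3-month visit: 3 × 365.25/12 = 91.3 days.
- Difference: 91.3 − 84 = 7.3 days, so the visit falls about a week after the last session. A delayed start could put the visit inside the programme.

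**Recall windows.** 3, 3 and 6 months. The last covers 6/12 = 50% of follow-up.

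**Mean delay from event to questioning.** Within a window of length L, evenly spread events wait L/2 on average, and each window is weighted by its share of the year.
- Visits at 3, 6 and 12 months: 0.25 × 1.5 + 0.25 × 1.5 + 0.50 × 3 = 2.25 months; maximum 6.
- Contacts at 3, 6, 9 and 12 months: 4 × 0.25 × 1.5 = 1.5 months; maximum 3.

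The whole gain from the extra contact is in months 6 to 12. Within the programme, events spread over 84 days have a mean time of day 42 and so wait 91.3 − 42 = 49.3 days on average under either schedule. Only a source other than a 3-monthly question shortens that delay.

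**Can the trial-level rule still act?** It counts SAEs over all patients. If recruitment is uniform over R months (the article gives no duration), the share not yet enrolled at the first patient's 3-month visit is (R − 3)/R:

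| Assumed R (months) | Not yet enrolled |
|---|---|
| 6 | 3/6 = 50% |
| 12 | 9/12 = 75% |
| 24 | 21/24 = 88% |

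Even on visit data alone, the rule could take effect while later patients are still to be exposed.

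**The case against.** The strongest reply is that the article says where events are asked about, not that nothing is captured elsewhere. It condenses a fuller protocol, and the additional files, including the data collection schedule and the cost questionnaire, are not at hand. Routes and timelines for SAE reporting are commonly left to such documents, so their absence here is no fault. That stands. It does not remove the point, which concerns the collection method the article does fix.

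Three stronger readings are tempting, and the document supports none of them.

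- A reader might infer that the SAE rules cannot operate during the programme. The individual rule is triggered by the event and not by a visit, staff see CONNACT patients weekly to week 8, and the trial-level count builds up over staggered enrolment, as the table shows.
- A reader might infer that about 20 of the 100 patients would have no safety data. The 20% is a sample-size allowance for missing data, not a forecast of lost AE reports, and a patient who misses one visit can be asked at the next.
- A reader might infer that the arms are already assessed unequally. The stated method is the same in both. The imbalance would arise only from informal reporting between visits, which the article neither describes nor excludes.

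It is also fair to say that exposure has no clean end at week 12 in both arms: usual-care physiotherapy has no set length, and CONNACT patients may continue exercising in a group. And the 2.25-month mean is a delay; it does not count missed events.

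**Conclusion.** The point holds as a weakness in the stated method with an inexpensive remedy. The only AE and SAE collection the article states is at 3, 6 and 12 months, the first at about the end of the 12-week programme and the last covering half of follow-up in one recall. That sits poorly with the aim of complete recording and with SAE rules that rely on timely knowledge.

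Its size is a mean delay to questioning of 2.25 months (maximum 6), against 1.5 months (maximum 3) with 3-monthly contacts. This rests on evenly spread events and on questioning being the route by which events become known. The programme-period timing also assumes a start at baseline. The number of SAEs that would be missed or learned of late cannot be estimated, because the document gives no event rate. The KOOS_4_ analysis is not affected.

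**What to change.** In the adverse-events paragraph under General outcomes:

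1. Identify hospitalisation SAEs for every randomised patient in both arms from the hospital administrative data already planned for costs. State when extracts are run: only extracts taken during follow-up can shorten the delay in the programme weeks; a single one at the end would improve completeness alone.
2. Ask the same AE question at each 3-monthly cost collection, including month 9.
3. Reconcile the two sources. Admissions for indicated knee surgery must be separated out, since the protocol does not count these as adverse events.
4. Base the between-arm comparison on these sources, which are identical in both arms.
5. Reconcile the collection schedule with the SAE rules in the same paragraph, leaving the rules themselves as they are, and say how events learned of between visits are recorded in each arm.

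The cost is one question at a contact already planned, reuse of a data extract, and some reconciliation work. Admissions to other hospitals, and life-threatening events without admission, will still depend on patient report.

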### Sample size calculation

The sample size needed to detect a 10-point difference between the intervention arm and usual care arm in KOOS_4_ was 41 patients in each arm based on a power of 90%, *p*-value of 0.05 (two-sided) and a standard deviation of 14. The anticipated population KOOS_4_ and standard deviations were based on the initial pilot study [25] done and the minimally clinically important difference on 10-points (MCID) for KOOS [24]. In order to account for a missing data rate of 20%, 100 patients will be recruited for the study.

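### The SAE definition omits lasting disability and does not name death, so a disabling injury treated without admission falls outside the SAE count and the safety review tied to it

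*Protocol article*

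**What the plan says.** All the relevant text is in one paragraph of the protocol article, Component 1, General outcomes.

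- **Definition:** "SAE will be defined as any AE that results in hospitalization or is life-threatening".
- **Collection:** AEs and SAEs "will be collected during all follow-up visits using open-probe questioning to ensure all AE are recorded". The Outcomes section places follow-up at 3, 6 and 12 months.
- **Consequence for the participant:** "Participation in the trial for the subject will cease if a SAE occurs".
- **Consequence for the trial:** "In the event of more than 3 SAE, decision to stop the trial will be considered", while "the final decision will be made by the Principal Investigator (PI) in conjunction with the ethics and clinical board".
- **The one stated exclusion from AEs:** "Undergoing an indicated surgical procedure such as a knee arthroplasty for knee OA due to failure of non-surgical treatment will not be considered an AE".

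The definition carries no wording such as 'including' or 'for example', and 'life-threatening' is not explained. No other section adds a criterion for seriousness.

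**The concern.** Seriousness here depends on the route of care (admitted or not) and on immediate danger to life. It does not depend on how lasting the harm is. The omitted category matters in this trial. Table 1 admits people aged 45 or over and allows walking aids. Table 2 gives every intervention patient eight group exercise sessions, and the self-management section adds home exercises. A fall or joint injury with lasting loss of function is a plausible harm of such a programme, and it can be managed without admission.

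Two things are at stake. First, such an injury would be reported among ordinary AEs, so the SAE tabulation would not show it. Second, the trial-level review is prompted by a count of SAEs, so the injury would not help to prompt it. The arms are also treated in different settings (community programme against hospital outpatient physiotherapy). A definition that leans on admission could therefore work differently by arm. The article has no data on this, so it is a possibility only.

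**Working it through.** The trigger of more than 3 SAEs is stated without a derivation, so there is no figure to reproduce. The check is mainly one of wording.

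**Step 1: apply the definition to four kinds of event.**

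| Event (as an AE) | Admission? | Life-threatening? | SAE as written? |
|---|---|---|---|
| Admission for any cause | Yes | Not needed | Yes |
| Death after admission | Yes | Not needed | Yes |
| Death outside hospital | No | Probably read as yes; not stated | Probably, by interpretation |
| Lasting disability, treated without admission | No | No | **No** |

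The last row follows from the text alone. The third row is ambiguous, not excluded.

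**Step 2: carry this to the trigger.** The trigger needs more than 3, that is, at least 4. Take three counted SAEs and one disabling injury treated without admission. As written the count is 3, and 3 is not more than 3, so no review is prompted. With disability among the criteria the count is 3 + 1 = 4, and review is prompted.

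**Step 3: check how a death would come to light.** AE collection is by questioning at follow-up visits, which a deceased participant cannot answer. Table 4 lists the CONSORT flow and reasons for withdrawal, and the economic evaluation uses hospital administrative databases. Either may reveal a death, but neither is named as a source of AEs.

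**Step 4: illustrate the size, on assumed inputs only.** The one input from the article is the planned total: "In order to account for a missing data rate of 20%, 100 patients will be recruited for the study". Assume that each participant contributes at most one SAE (in keeping with participation ending after an SAE), that a true proportion p has a serious event, and that the definition misses a share s of these. Then the counted number X is Binomial(100, p(1 − s)), and the quantity of interest is P(X ≥ 4).

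| Assumed p | s = 0 | s = 10% | s = 20% | s = 30% |
|---|---|---|---|---|
| 2% | 0.141 | 0.107 | 0.077 | 0.052 |
| 3% | 0.353 | 0.285 | 0.220 | 0.160 |
| 5% | 0.742 | 0.664 | 0.571 | 0.465 |
| 8% | 0.963 | 0.935 | 0.889 | 0.817 |

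For example, with p = 5% and s = 20%, p(1 − s) = 0.05 × 0.80 = 0.04, and the chance of reaching the trigger falls from 0.742 to 0.571, a drop of 0.171. Over the whole grid the drop runs from 0.028 (8%, 10% missed: 0.963 − 0.935) to 0.277 (5%, 30% missed: 0.742 − 0.465). Both p and s are assumptions. The table shows direction and sensitivity and does not estimate what will happen in this trial.

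**The case against.** A reader might infer more than the text supports, and the case against those stronger readings is good.

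- **That a death at home is non-serious.** The article does not say so. An AE that kills the patient was, on an ordinary reading, life-threatening, so it would most likely be counted. What stands is narrower: death is not named, the term that would cover it is not defined, and the stated collection route does not obviously reach it.
- **That such events go unrecorded.** They do not. All AEs are to be recorded, and Table 3 lists adverse events as an outcome. A disabling injury loses the serious label but stays in the data.
- **That the reported SAE rate by arm would be wrong.** It would be correct under the stated definition, which readers can see. It would simply not include lasting disability.
- **That the trial could fail to stop when it must.** The trigger does not compel stopping. It leads to consideration, with the decision left to the PI and the boards, and nothing in the text forbids an earlier look at a grave AE. This limits the consequence. It does not remove it, because an event outside the count does nothing to prompt the review.
- **That counting a brief, unrelated admission is itself a defect.** Any definition that keeps hospitalisation as a criterion does the same.

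It can also be said that an article leaves operational detail to the full protocol. That is fair for how deaths are ascertained. It does not answer the main point, because the article states the definition outright. The strongest practical objection is that widening the definition has side effects, since an SAE also ends participation. That objection stands and shapes the fix.

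**Conclusion.** The point holds in a limited form. The definition is closed and has two criteria. A disabling injury that is neither life-threatening nor admitted is not an SAE and does not count towards the review at more than 3 SAEs. This follows from the wording and needs no assumption. The status of a death outside hospital is a drafting ambiguity, with inclusion the likelier reading.

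The size cannot be stated, because the article gives no rate of deaths, injuries or SAEs. Only the sensitivity of a small count can be shown: one event can move the total from 3 to 4. The probabilities above rest wholly on assumed rates and assumed missed shares. The point concerns classification and safety reporting and does not affect the analysis of the primary outcome. It should be corrected because the repair is short and the definition feeds a trial-level safety review.

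**What to change.** Add two criteria to the definition for classification and reporting: that the AE results in death, and that it results in persistent or significant disability or incapacity. State that vital status is checked from the records for any participant who misses a follow-up visit.

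In the same amendment the sponsor must reconcile two neighbouring sentences with the revised definition: the one ending a subject's participation after any SAE, and the one tying trial review to the SAE count. Both now operate on the narrower definition. No threshold and no rule on ending participation is proposed here.

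**Cost:** a sentence or two in the protocol, a matching field on the case report form and a records check for missed visits. A few more events will be classified as serious, and the review count may be reached sooner. Unless the sentence on ending participation is reconciled, a few more participants would also leave the trial, which would add to missing outcome data.
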